### Assessment and follow-up

Pre-treatment assessment is performed by routine examinations including a physical examination, standard laboratory tests, a CT scan of the thorax and abdomen (or PET/CT), upper gastrointestinal contrast, upper endoscopy with biopsies and endoscopic ultrasound. For patients who had received preoperative neoadjuvant treatment, they will be restaged and confirmed to suitable for surgery by clinicians.

After surgery, follow-ups will be performed one time per 3 months in the first two years and one time per 6 months from the third year until the end of follow-up. Examination will be focused on laboratory tests (blood routine, tumor biomarker), CT scan, ultrasound, and quality of life questionnaires. For all patients, follow-up is carried out until the end of the trial or death.

### Statistical analysis

Statistical analyses are performed using SPSS version 20.0 software (SPSS Inc. Chicago, Illinois, USA). Survival will be estimated by Kaplan-Meier methods and analyzed using log-rank test. Complications will be calculated as percentage with 95% confidence intervals and analyzed by χ^2^ test or Fisher’s exact test. Student’s *t* test and analysis of variance (ANOVA) test was conducted for the comparison in continuous variables, while χ^2^ test or Fisher’s exact test was used in categorical variables. *P* < 0.05 is set as the significance level.

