## Methods

### Study design

This is a prospectively randomized controlled trial to assess the comparison between RAE and MIE in the treatment for patients with ESCC. According to previous studies, the long-term survival results of RAE seemed to be comparable but not inferior to the MIE or open esophagectomy [19, 20]. Therefore, the present study was designed as a non-inferiority trial, which was based on the hypothesis that the 5-year overall survival in the RAE is uncompromised with MIE. To achieve the primary goal, 360 patients with ESCC will be recruited from 4 high-volume centers (> 100 cases of combined approaches annually) in China. Based on the volume of esophagectomy in our center, 120 patients will be scheduled for this trial and approximately 5 patients will be enrolled for each group per month. For the other three centers, the estimated enrolled patients will be 2 for each group per month. The flow chart of this trial is presented in Fig. 1. The study has been approved by the ethics committees of participating institutions, as well as in accordance with the principles of the Declaration of Helsinki and Good Clinical Practice Guidelines. Written informed consent is obtained from each participant.

Neoadjuvant therapy will be used as a stratification factor in this study. After finishing preoperative treatment, patients will be restaged and confirmed to suitable for surgery by multidisciplinary team (MDT) of clinicians. When the tumor is considered as resectable, patients will undergo the randomized intervention - either RAE or MIE depending on randomization.

The study started on July 2017. Enrollment will take about 2 years and follow-up for will be 5 years. So the total duration of this study will lasts 7 years.

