### Inclusion criteria

Age ranges from 18 to 75 years;European Clinical Oncology Group Performance Status (ECOG PS) 0–2;Histological subtype of esophageal squamous cell carcinoma;Primary tumors are located at the intrathoracic esophagus;Pre-treatment stage as cT_1-4a_N_0-2_ M_0_ (AJCC/UICC 7th Edition);Didn’t receive any therapy including chemotherapy or radiation for other cancers;Written informed consent.

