### Sample size considerations

The sample size was calculated based on the primary outcome overall survival. A non-inferiority trial is planned in which the primary analysis will use the non-inferiority log-rank test. Generally, non-inferiority margins in local-advanced cancers were in a narrow range (1.18–1.33) according to the FDA’s estimate [21]. After extensive discussion, the researchers have decided that the upper bound on non-inferiority is 1.33. The total trial will take about 7 years which consists of 2-year recruitment period and 5-year follow-up period. We estimated a missing rate of 5% per year in each group. A hazard rate of 0.60, a power of 0.80 and a significance level of 0.05 will be used. Based on the assumptions, a sample size of 360 (2 × 180) participants was calculated using PASS 11 software (NCSS, LLC; Version 11.0.7).

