### Randomization

Randomization will be performed via a computer-generated random numbers sequence and further stratified by whether the patient has undergone neoadjuvant treatment or not. Considering the unfeasibility in clinical practice, no blinding will be set for the patients and surgeons. Nevertheless, the independent study team is blinded to the allocation.

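### Overall survival is compared by a plain log-rank test that ignores pre-treatment clinical stage; a stage-stratified Cox hazard ratio should be prespecified for the 1.33 margin

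*Protocol article*

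**What the plan says.** All references are to the protocol article.

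- **Eligibility (Inclusion criteria):** "Pre-treatment stage as cT_1-4a_N_0-2_ M_0_ (AJCC/UICC 7th Edition". This covers early node-negative to locally advanced node-positive disease, and stage must be established before a patient can enter.
- **Allocation (Study design; Randomization):** "Neoadjuvant therapy will be used as a stratification factor in this study", and the sequence is "further stratified by whether the patient has undergone neoadjuvant treatment or not". Stage is not a randomisation factor.
- **Primary test (Sample size considerations):** "the primary analysis will use the non-inferiority log-rank test", with the margin given as "the upper bound on non-inferiority is 1.33".
- **Survival analysis (Statistical analysis):** "Survival will be estimated by Kaplan-Meier methods and analyzed using log-rank test". No stratum or covariate is named.

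The article does not say whether 1.33 is a population-average HR or an HR among patients of the same stage.

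**The concern.** Clinical stage is a natural prognostic variable for survival after esophagectomy, and it is fixed before allocation. A test that ignores it has two consequences in a non-inferiority trial.

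1. **Chance imbalance.** Stage will differ somewhat between two arms of 180. The plain test cannot separate that difference from an effect of the operation, so a lower-stage RAE arm makes a non-inferiority claim easier.
2. **Attenuation.** The HR is not collapsible. Leaving out a strong prognostic factor moves it towards 1 even when the arms are perfectly balanced. That works against the claim in a superiority trial and in favour of it here.

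If an imbalance favouring RAE appears and no adjustment was prespecified, a non-inferiority claim is open to challenge, and a covariate chosen after seeing the imbalance would not be credible.

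**Working it through.** **1. The plan's own figure.** Inputs from Sample size considerations: margin 1.33, hazard 0.60 (read as per year), power 0.80, alpha 0.05 (sidedness not stated), 5% yearly loss, 2 years of recruitment and 5 of follow-up.

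- Events = 4 × (1.645 + 0.842)² / (ln 1.33)² = 305 at one-sided 0.05.
- With loss hazard −ln 0.95 = 0.0513, the total hazard is 0.6513. The event probability is (0.60/0.6513) × [1 − (e^(−0.6513(T−2)) − e^(−0.6513T))/(2 × 0.6513)].
- T = 5 years in all: 0.848, so N = 360, as stated. T = 7 years as written: 0.901, so N is about 338.
- At one-sided 0.025, N is about 430. The stated 360 therefore points to one-sided 0.05, which is used below.

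**2. Can stage imbalance alone produce a claim?** With 305 events, SE(log HR) = 2/√305 = 0.1145. A claim needs an observed HR of at most 1.33 × e^(−1.645 × 0.1145) = 1.10, a shift of 0.188 on the log scale from a true 1.33.

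The article gives no stage mix or stage effect. Assumed: three stage groups of 35/40/25%, stage HRs 1:1.7:2.9 (moderate) or 1:2.5:5 (strong), and neoadjuvant use of 5/40/80% by stage. With allocation stratified by neoadjuvant use, the SD of the between-arm difference in mean log hazard due to stage is 0.035 (moderate) or 0.054 (strong).

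- SDs needed: 0.188/0.035 = 5.4, or 0.188/0.054 = 3.5.
- A 2-SD imbalance moves 1.33 only to 1.33 × e^(−0.070) = 1.24, or 1.33 × e^(−0.108) = 1.19.

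**3. Error rates by simulation.** N = 360, 1:1, allocation stratified by neoadjuvant use, the loss and follow-up above (7 years), and non-inferiority if log HR + 1.645 SE < ln 1.33. Two mean hazards were used: the stated 0.60, and 0.12 per year. The second is there because the Discussion cites 59% 5-year survival with MIE, whereas 0.60 per year gives e^(−3) = 5%; e^(−0.12 × 5) = 55% is closer.

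False non-inferiority when the **within-stage** HR is 1.33 (2,500 trials per row; Monte Carlo SE about √(0.05 × 0.95/2500) = 0.4 points):

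| Hazard | Stage effect | Mean unadjusted HR | Plain | Stage-stratified |
|---|---|---|---|---|
| 0.60 | moderate | 1.29 | 7.8% | 5.2% |
| 0.60 | strong | 1.26 | 12.7% | 5.6% |
| 0.12 | moderate | 1.31 | 6.6% | 5.6% |
| 0.12 | strong | 1.29 | 7.0% | 4.8% |

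False non-inferiority when the **population-average** HR is 1.33 (4,000 trials per row; the tenths are ranked by stage imbalance):

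| Hazard | Stage effect | Plain | Stage-stratified | Plain, tenth most favourable to RAE | Plain, tenth least favourable |
|---|---|---|---|---|---|
| 0.60 | moderate | 5.1% | 2.7% | 10.5% | 1.5% |
| 0.60 | strong | 4.4% | 1.3% | 12.8% | 1.0% |
| 0.12 | moderate | 4.5% | 3.7% | 7.5% | 1.5% |
| 0.12 | strong | 4.7% | 3.3% | 11.0% | 1.2% |

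Power at HR 1, plain against stage-stratified, in the same row order: 82.1 and 81.6%; 79.6 and 76.7%; 56.0 and 54.9%; 55.2 and 54.4%.

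**4. Cause of the excess in the first table.** With allocation balanced on stage itself, the mean unadjusted HR was still 1.31 for a within-stage HR of 1.33. The excess is non-collapsibility, not chance imbalance.

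**5. Does the neoadjuvant stratum suffice?** Other assumptions: stage groups 30/40/30%, relative hazards 0.5:1:2 or 0.3:1:2.5, the same neoadjuvant use by stage, MIE 5-year survival 59%, within-stage HR 1.33, 4,000 trials each.

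- Overall false non-inferiority: plain 6.1 and 8.5%; stratified by neoadjuvant use 5.8 and 7.9%; stratified by stage 4.9 and 5.2%.
- Where stage favoured RAE by more than 1 SD: 12.6 and 19.0%; 12.1 and 17.8%; 5.5 and 5.7%.
- Power at HR 1: plain 53–54%, stage-stratified 53%.

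Under these assumptions, using the existing stratum removes little of the problem. Simulations under a further set of assumed stage effects gave 5–7% for the plain test against 4–5% with stage strata.

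**The case against.** **Scope.** Covariates are often left to the statistical analysis plan, which is not shown, and an unadjusted log-rank test contradicts nothing in the article. It stands that the omission is not an error and that the analysis plan may add stage. But the article does state a primary test, in two sections, and a better one is available from data that eligibility already requires.

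**The stronger reading.** A reader might infer that chance stage imbalance can turn a truly inferior result into a non-inferiority claim, or that the plain test exceeds its error rate for that reason. The documents do not support this. Imbalance under randomisation is symmetric and already counted in alpha: at a population-average HR of 1.33 the plain test errs in 4.4–5.1% of trials, and the raised rates in the favourable tail are offset by 1.0–1.5% in the opposite one. Imbalance alone would need 3.5 to 5.4 SD.

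**The margin.** Attached to a log-rank test, 1.33 most naturally means a population-average HR, and on that reading there is no overall excess. This stands. The excess arises only if 1.33 is meant within stage, which the article leaves open.

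**Assumed stage effects.** Nothing in the article quantifies them. Pre-treatment stage may also predict less in patients who are restaged after neoadjuvant therapy, with survival counted from surgery. That limits the size of the benefit, but a weak stage effect also makes adjustment nearly costless.

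**Conclusion.** The point holds as a recommendation on the choice of analysis, not as a finding that the planned test is invalid.

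- **Margin read as population-average:** the plain test is nominal overall. Its weakness is that the result in the one trial run depends on how stage happens to fall.
- **Margin read within stage:** the plain test raises false non-inferiority to about 5–8% in most settings, against about 4–5% with stage strata (up to 5.6% in single settings, within Monte Carlo error of 5%). The one larger figure, 12.7% against 5.6%, needs both the strong stage effect and the stated hazard of 0.60 per year.
- **Power:** no material change in most settings. The largest loss was 2.9 points, in that same extreme setting.

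All of this rests on one-sided 0.05, inferred from the sample size, and on assumed stage mix, stage effects and neoadjuvant use.

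**What to change.** Prespecify, before survival by arm is examined:

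1. Non-inferiority is read from the upper confidence limit of a Cox HR stratified by, or adjusted for, pre-treatment clinical stage (for example cT1–2 against cT3–4a, and cN0 against cN+) together with the neoadjuvant stratum, compared with 1.33.
2. The HR, and so the margin as applied, is conditional on stage.
3. The unadjusted log-rank test is kept as a sensitivity analysis.
4. Disease-free survival is treated the same way.
5. Pathological stage is not a covariate. The Discussion cites retrospective studies in which RAE yielded more nodes than MIE, so pathological staging may itself depend on the allocated operation.

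If the statistical analysis plan already adjusts for stage, the primary test named in the article needs to be reconciled with it.

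The cost is wording only, since eligibility already requires the stage data. The downside is some conservatism if 1.33 was meant as a population-average HR: false non-inferiority of 1.3–3.7% in the check instead of 5%. The two example splits with the neoadjuvant factor give eight strata, 360/8 = 45 patients each on average; if some prove sparse, covariate adjustment serves the same purpose.

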**Discussion:**

This is the first prospectively randomized controlled trial designed to compare RAE with MIE as surgical treatment for resectable ESCC. According to our hypothesis, RAE will result in at least similar oncologic outcomes and long-term quality of life, but with a shorter operation time, lower percentage of perioperative complications, lower blood loss, and shorter hospital stay when compared with MIE. This study started in July 2017. Follow-up will terminate after 5 years from the time when the last patient was enrolled.

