#### Secondary endpoints

5-year disease-free survival (DFS) time: DFS is defined as the time from the date of surgery to the day of tumor recurrence, tumor progression or patients’ death assessed up to 5 years [24].3-year OS and DFS.Quality of life (QOL): QOL is assessed among patients by using the European Organization for Research and Treatment of Cancer Quality of Life Questionnaire C-30 (EORTC QLQ-C30) and EORTC QLQ-OES18 at randomization, and 3 month, 6 month, 9 month and yearly till 3 years after surgery respectively.Short-term outcomes: Short-term outcome refers to operation related index during the perioperative period, which includes operative time, total blood loss, R0 resection rate, total and positive numbers of dissected lymph nodes, 30- and 90-day postoperative mortality, length of hospital stay and ICU stay, postoperative recovery, and the incidence of treatment-related complications. True operation time is defined as time from incision until finally closure (minutes), and in which the time of docking and undocking robot was removed. We also assess the total operative time in which docking and undocking time was included. Postoperative recovery is defined as the days of chest tube and other surgical drainages removed, and the days until first ambulation and oral intake. First ambulation was defined as when the patient could continuously walk for at least 10 m, and first oral intake was when the patient could first eat gelatin or semi-solid food. The complications were diagnosed and defined according to the International Consensus of Esophagectomy Complications Consensus Group (ECCG) [25] (shown in Table 1).

**Table 1 Tab1:** Definitions of complications

Pulmonary	
Pneumonia: Radiographic confirmation with positive respiratory tract culture.	
Pleural effusion: Pleural effusion requiring additional drainage procedure.	
Pneumothorax: Radiographic confirmation requiring chest tube reinsertion.	
Respiratory failure: Reintubation or tracheostomy for weaning failure.	
Atelectasis: Atelectasis mucous plugging requiring bronchoscopy.	
Cardiovascular	
Cardiac arrest requiring CPR	
Atrial arrhythmia: Electrocardiographic (ECG) confirmation of atrial arrhythmia.	
Deep venous thrombosis: Ultrasound confirmation of deep venous thrombosis.	
Myocardial infarction: Confirmed by ECG changes, information with cardiac biomarkers and symptoms of ischaemia.	
Gastrointestinal	

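### The only method stated for continuous outcomes, t test/ANOVA, fits the repeated quality-of-life scores poorly; a baseline-adjusted longitudinal analysis should replace it for that endpoint

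*Protocol article*

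**What the plan says.** The Statistical analysis section of the protocol article names Student's t test and says that an "analysis of variance (ANOVA) test was conducted for the comparison in continuous variables"; P below "0.05 is set as the significance level". No other method for a continuous outcome appears in the article. The same section promises 95% confidence intervals for complications but mentions none for continuous variables.

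Quality of life is a secondary endpoint, and the abstract also lists it in the primary objective. The Secondary endpoints section uses the "Quality of Life Questionnaire C-30 (EORTC QLQ-C30) and EORTC QLQ-OES18", completed "at randomization, and 3 month, 6 month, 9 month and yearly till 3 years after surgery respectively". That is one baseline and six later assessments (3, 6, 9, 12, 24 and 36 months).

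The abstract's Discussion states the expectation that "RAE will result in at least similar oncologic outcomes and long-term quality of life", and the main Discussion repeats it. The Randomization section stratifies by neoadjuvant treatment.

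**The concern.** Quality-of-life scores are continuous, repeated and have a baseline. A t test or one-way ANOVA is built for a single independent measurement per patient. If the general rule is carried over to these scores, three things are at stake.

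- **Precision.** The baseline score is collected at randomization, and a visit-wise test makes no use of it.
- **Who is compared.** Each later visit would compare a smaller and more selected group than the one before, because some patients have died and others have not returned a questionnaire.
- **What can be concluded.** The stated expectation is similarity or better. A difference test judged at P < 0.05, with no interval, cannot support that: a non-significant result is compatible with a real deficit.

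**Working it through.** The article gives no sample size, standard deviation, effect size or power for quality of life, so there is no planned figure to reproduce. The check takes each way the stated method could be applied and compares it with baseline adjustment.

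**Inputs**
- 180 patients per arm (Sample size considerations).
- Six post-baseline assessments, the last at 36 months (Secondary endpoints).
- Loss of 5% per year per arm, stated for the survival calculation (Sample size considerations).
- 5-year survival of 59% with MIE, from a comparative study cited in the Discussion. It is not the trial's planning input.
- A hazard rate of 0.60 (Sample size considerations). Its time unit is not given.
- *Assumed:* correlation r between baseline and follow-up score of 0.3 to 0.6, equal variances at the two times, and constant hazard.

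**Step 1. Variance of the between-arm difference at one visit, relative to a t test on follow-up scores**

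| Analysis | Formula | r = 0.3 | r = 0.5 | r = 0.6 |
|---|---|---|---|---|
| t test, follow-up score only | 1 | 1.00 | 1.00 | 1.00 |
| t test, change from baseline | 2(1 − r) | 1.40 | 1.00 | 0.80 |
| Baseline-adjusted | 1 − r² | 0.91 | 0.75 | 0.64 |

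Compared with the follow-up-only test, adjustment cuts variance by 9% (1 − 0.91) to 36% (1 − 0.64). In patients, 1/0.91 = 1.10 and 1/0.64 = 1.56, so the gain is worth 10% to 56% more patients.

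Change scores do not close the gap: 2(1 − r) − (1 − r²) = (1 − r)², which is never negative. Below r = 0.5 a change-score test is less precise than ignoring the baseline altogether.

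As an illustration only, take a true difference of 0.3 SD (assumed), all 180 per arm contributing and two-sided 0.05. The follow-up-only t test then has 81% power. With adjustment, power is 85% at r = 0.3 and 94.5% at r = 0.6.

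**Step 2. How many patients could contribute at 36 months**

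With 59% alive at 5 years:
- annual hazard = −ln(0.59)/5 = 0.1055
- alive at 3 years = exp(−3 × 0.1055) = 0.73, so about 27% have died
- not lost at 5% per year = 0.95³ = 0.857
- alive and retained = 0.7286 × 0.857 = 0.625, or about 112 of 180 per arm

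If instead 0.60 is an annual hazard:
- alive at 3 years = exp(−1.8) = 0.165
- alive and retained = 0.165 × 0.857 = 0.142, or about 26 of 180 per arm

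The share missing at 36 months is therefore about 38% on the first reading and 86% on the second, before any questionnaire non-return among patients still followed.

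**Step 3. Classical repeated-measures ANOVA**

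This reading would use all visits, but it requires a complete set of scores. A patient who dies before 36 months or misses one questionnaire leaves the analysis entirely, including the early visits. The 36-month figures in Step 2 are thus upper limits on the number analysed: about 112 per arm on the more favourable reading.

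**The case against.** The strongest reply is that the quoted sentence is general and never mentions quality of life. It fits operative time, blood loss, node counts and length of stay well. A condensed article may leave the longitudinal model, the covariates and missing-data handling to a full protocol or analysis plan that is not shown here. That absence is not an error, and this point does not rest on it. It rests on the one method the article does state, which by default reaches these scores.

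A reader might infer more, namely that the plan discards the baseline and handles drop-out by testing survivors at each visit. The document does not say so. It does not specify raw scores, change scores or visit-wise testing, and it is silent on missing questionnaires and on death. A t test can use change scores and ANOVA can be repeated-measures. Those readings are fair, but Steps 1 and 3 show that neither does as well as baseline adjustment with all available visits.

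A reader might also infer that a P value above 0.05 will be presented as similar quality of life. No section says this. The article states an expectation without a decision rule, and its formal non-inferiority margin of 1.33 concerns overall survival only. What stands is narrower: the stated difference test could not support that expectation.

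Two further objections hold in part. The variance gain is general arithmetic on assumed correlations, not evidence from this trial. And a mixed model does not by itself solve truncation by death, because it implicitly projects scores beyond it.

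**Conclusion.** The point holds in a limited form. The t test/ANOVA rule is the only method the article offers for scores measured at baseline and six later visits, and every way of applying it falls short of a baseline-adjusted longitudinal analysis. The loss is a 9% to 36% variance reduction forgone against a follow-up-only comparison, if r lies between 0.3 and 0.6 and variances are similar. Attrition by 36 months is material on either reading of the article's inputs (about 38% or 86% per arm). These figures rest on constant hazard and on applying the survival calculation's loss rate to questionnaires.

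The documents do not support saying that the plan has chosen to ignore the baseline, has adopted a survivors-only rule, or will treat non-significance as similarity. The point concerns a secondary endpoint and leaves the overall survival analysis untouched. The change is worth making because it uses data already being collected.

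**What to change.** For quality of life, replace the general rule with the following:

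- One longitudinal mixed model per scale, with arm, visit, arm-by-visit interaction, baseline score and neoadjuvant stratum.
- Adjusted mean differences with 95% confidence intervals at named visits.
- A statement that the results describe patients while alive, with deaths per arm reported alongside at the same visits. The model alone does not settle this.
- Any statement that quality of life is similar or better to be based on the confidence interval, not on a non-significant P value.

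The t test can stay for the single-measurement perioperative outcomes.

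The model needs a fixed list of visits. The Assessment and follow-up section places questionnaires within visits held "one time per 3 months in the first two years and one time per 6 months from the third year", which gives 8 + 2 = 10 visits by three years against six in the endpoint section. The two sections should be reconciled.

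The cost is a change of wording and slightly more programming. The analysis also takes on a missing-at-random assumption for missed questionnaires, which should be stated. No new data are required.
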